#### Analysis

The analytic strategy for TEC will be focused on assessing the effectiveness of the PCC intervention by comparing the PCC intervention group to the control group. The unit of randomization is healthcare facility and the unit of analysis is the individual. To test the effectiveness of the

intervention, we will use a standard stepped-wedge analytic approach (Hussey & Hughes, 2007) based on a generalized linear mixed model (GLMM) where facility is included as a random effect and period is included as a fixed categorical variable to adjust for secular trends. Due to a ramp up in intervention effect, we will determine code three different groups for the intervention analysis (control, early intervention ( $\leq 6$  months), late intervention ( $> 6$  months), fit as separate categories or ordered (Hughes et al., 2015; Kenny et al., 2021)). This decision is based on contextual experience in the facilities and anticipation that there will be a lag in seeing the benefits from training, mentoring, and data feedback (e.g., the first data feedback only occurred 3 months into the intervention). Furthermore, we will explore alternative parameterizations for secular trends including linear and cubic splines. If these alternative parameterizations better describe variability in the data (as determined by standard model fit statistics such as Akaike's Information Criterion [AIC]) then the model will be updated to reflect this accordingly. Distributions and link functions used will depend on the outcome (see outcome-specific sections below for more details).

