Analysis: This analysis will include data from all studies leveraging the full stepped-wedge design. The 6-month period prior to study start will be included as a Period 0 when all facilities are control. We will use mixed effects logistic regression, accounting for clustering at both the individual- and the facility-level using random effects. The main exposure will be exposure to the PCC intervention and will be assigned at the visit level. As some individuals may be seen more than once during the study period and cross-over from control to intervention, each visit will be categorized as control or intervention based on when it occurred (e.g., an individual may have one visit assigned as control and a later visit categorized as intervention). Due to a potential lag in intervention effect, we will code intervention periods as control, early intervention ( $\leq 6$  months), and late intervention ( $> 6$  months) (Hughes et al., 2015; Kenny et al., 2021). To account for potential imbalances due to cluster randomization at baseline and also increase precision, we will adjust for individuals' care status at enrollment (in care, new ART, LTFU), sex, age, time in care, baseline clinic-level retention (i.e., percent of visits where patient was more than 30 days late to their next appointment assessed in the 6 months prior to study start), and randomization strata (initial cluster randomization stratified by facility size and viral load coverage based on programmatic data). Facility will be included as a random effect. We will consider including the following potential confounders due to imbalance in randomization: WHO severity groups, marital status, and education. We will use standard model diagnostic procedures and consider alternate specifications as needed if we face challenges with standard statistical issues such as model convergence or overfitting. We will use marginal estimation commands to report absolute and relative risk differences under treatment versus control conditions.

In addition to the overall analysis, we will perform stratified analyses to assess changes specifically across:

- Care Status at time of visit (in care, new ART, LTFU)
- Sex
- Age (<25, 25-44, >45)
- Advanced HIV Disease at enrollment in care (WHO Stage 3 or 4, CD4<200) – Dependent on adequate coverage of CD4 measurements
- Clinic Size and Type

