## **7.0 STEPPED WEDGE DESIGN**

Stepped-wedge cluster randomized designs are used when equipoise is not met (because the preponderance of evidence favours the intervention), but when there is also a desire for rigorous inference about the magnitude of the effect (50). We plan on evaluating approximately 34 facilities mainly in Lusaka Province which are between 500 and 10,000 patients currently on ART. We will roll out the intervention in four groups, at time zero, 6, 12 and 18 months, and follow all sites for a total of 24 months. We employ an open-cohort design where new patients can enter observation time at any time during the trial and be measured for outcomes at multiple times. Some measurements which are made repeatedly overtime, and in these cases, it is possible that a single patient if surveyed more than once can contribute to the patient experience or service delivery outcomes both before and after cross over. For other outcomes such as retention and viral load which represent cumulative effects of longitudinal exposure to the intervention, we will censor at crossover. Because we seek to detect both the impact of the intervention on the patient experience (which can occur over shorter term) as well as retention and viral load (over a longer term), we will weight the steps unequally to achieve adequate power in both types of outcomes. Specifically we seek to randomize approximately 75% of facilities to the first and last waves and 25% to waves two and three.

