### *Differences in patient experience as measured by exit interview*

We will assess changes in the mean level of satisfaction using a validated composite of the questions from the patient exit surveys. We will use mixed effects linear regression with clustering at the facility level to estimate the effect of the intervention on change in the patient satisfaction with their clinic visit. We will also assess changes in patient responses on key component variables such as proportion who report being happy with their visit, witnessing rude behavior, and having missing laboratory data using mixed effects linear or logistic regression, as appropriate. We will use the Hussey-Hughes method to account for the stepped-wedge study design.

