We will be training patients to be QIP in order to get an objective review of patient experience in the clinic. QIP will present as per usual for their routine care in their ART clinic but will be trained in the exit interview and SMS instruments. This is because in the context of Zambian HIV care and treatment program, patients cannot rotate through facilities without disrupting systems. With QIP undergoing routine without any simulation or manipulation, many ethical protections are provided – the length of the appointment would be appropriate, clinical resources and time would not be wasted, patients will not be exposed to unnecessary costs, procedures and treatment, and the interaction will be relevant, credible, practical and safe. Hence, patients will be trained not to alter their behaviour and not to manipulate the interaction in any way to allow for collection of more complete and accurate data on patient experience. Using up to 50 patients for 100 observations will also provide information on diverse experiences based on type of visit, day of the week, number of HCWs involved in the interaction, and patient volume. Patients who express interest in serving as QIP will be asked for their consent informed by full disclosure including on associated risks (16). To further protect patient and provider privacy, exit and SMS interviews conducted by QIP will be presented as aggregate data containing no personal identifiers.

Patient tracing will follow the tracing procedures that are currently implemented in standard clinical practice. This includes finding the patients, identifying their outcomes, and encouraging them to return to care. When relevant, this also means speaking with family members of the deceased to determine the patient outcome. As demonstrated by the Better Info Study, we conduct tracing with the utmost care and concern for patient confidentiality. This includes practices such as training of patient tracers, stating only health-related purposes or other socially acceptable, non-identifiable reasons for any visit, and consulting health care workers and key stakeholders at the study-affiliated clinics to identify other important tracing practices to maintain confidentiality. Any further activities occur only if informed, voluntary consent is granted by the potential participant.

The following sub-sections elaborate the human subject protections by which this study will abide.

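### One patient may give several experience surveys, but the planned models have no patient level, so standard errors could be off in either direction

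*Combined protocol and SAP*

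**What the plan says.** Protocol section 7.0 describes the sampling frame for all outcomes: "We employ an open-cohort design where new patients can enter observation time at any time during the trial and be measured for outcomes" repeatedly. For surveys it adds the possibility that "a single patient if surveyed more than once can contribute to the patient experience or service delivery outcomes both before and after cross over".

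The patient-experience models do not carry that structure:

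- SAP 4.0 (TEC, the SAP's only patient-experience outcome): "facility is included as a random effect and period is included as a fixed categorical variable to adjust for secular trends". There is no patient term. GEE is mentioned only as a fallback for convergence problems, with no clustering level named.
- Protocol 8.6, exit interviews: "We will use mixed effects linear regression with clustering at the facility level to estimate the effect of the intervention". The trained-exit paragraph that follows also clusters by facility only.

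By contrast, the missed-visit model in SAP 5.2 is specified as "accounting for clustering at both the individual- and the facility-level using random effects", because people are seen more than once and cross over.

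The documents disagree on how many surveys a trained patient gives. The Figure S1 legend calls client experience a cross-sectional assessment, the SAP 4.0 survey table counts 1,200 patients, and protocol 8.6.1 plans about 15 people for 15 encounters per clinic. Protocol 9.0, on the same trained-patient method, speaks of "Using up to 50 patients for 100 observations".

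**The concern.** Two surveys from one person are correlated beyond what they share through the clinic. A model with only a facility effect treats them as independent. The point estimate stays essentially unbiased, but its standard error does not match its sampling variability.

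The direction depends on where the repeats fall. Two surveys by one person in the same clinic and period carry less information than two people would, so the planned interval is too narrow. When the same people appear in different periods, person-to-person variation partly cancels out of the before-after comparison, so the planned interval is too wide. The missing level is the patient, which is a separate matter from any facility-by-period effect.

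**Working it through.** **Inputs from the documents.** TEC layout from the SAP 4.0 table: wave 2 (4 clinics) 30/30/15/15 surveys per clinic over the four periods, wave 3 (4 clinics) 15/15/15/15, wave 4 (8 clinics) 15/15/30/15; total 1,200. Baseline 65% positive, ICC 0.2, 80% power, 5% level (taken as two-sided). Exit surveys: minimum 4,000 in total (protocol 8.6.2), or 75-100 per clinic per period (8.2.2), about 34 clinics of 500 to 10,000 patients.

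**Assumed, because not given.** Share s of surveys that are repeats, and within-person correlation ρ = 0.3-0.5 of the residual after the clinic effect.

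**1. The plan's own figure.** With the Hussey-Hughes variance on facility-period means, one intervention term, variance 0.65 × 0.35 and 15 surveys per clinic-period (16 × 4 × 15 = 960), the SE is 5.24 points. Detectable difference = (1.960 + 0.842) × 5.24 = 14.7 points, with 81.7% power at 15 points. This reproduces the stated 15.0 points. The unequal cells (1,200) give SE 4.55 and 12.7 points. Both treat every survey as a different person.

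**2. Effect of repeats on the TEC standard error.** The planned covariance of a clinic's four period means is τ² in every entry plus σ²/n on the diagonal. Repeats within a period add σ²ρs/n to the diagonal. Repeats across periods a and b add σ²ρs·min(nₐ,n_b)/(nₐn_b) off the diagonal. The true SE of the planned estimator is the sandwich form under this covariance. Model terms: period, early and late intervention.

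| Repeats | Planned SE ÷ true SE |
|---|---|
| None | 1.00 |
| 25% across periods, ICC 0.2 | 1.03-1.06 |
| 25% within clinic-period, ICC 0.2 | 0.945-0.967 |
| 25% of each, ρ = 0.4, ICC 0.2 | 0.99-1.00 |
| Everyone twice within a period, ICC 0.05-0.2 | 0.82-0.90 |
| Same 15 people every period, ICC 0.05-0.2 | 1.08-1.26 |

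Hand checks: with everyone twice in a cell, the variance of its mean rises by the factor 1 + ρ, and 1/√1.3 = 0.88, 1/√1.5 = 0.82. For a difference between two equal-sized periods with s = 0.25 and ρ = 0.4, √(1 − 0.1) = 0.95, against 0.955 from the full calculation for a single intervention term. A simulation with REML fits gave 0.82-0.90 for everyone twice in a period and 6-25% too large for the same people every period.

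For a single intervention term at s = 0.25 and ρ = 0.4, the detectable difference moves from 12.7 to 12.2 points (across periods) or 13.4 points (within period). Repeats in the same condition but in adjacent periods, at up to half a cell, change little: true/model ratio 0.99-1.03.

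**3. Type I error.** At a ratio of 0.945-0.967 the nominal 5% test rejects when |Z| exceeds 1.96 × 0.945 = 1.85 to 1.96 × 0.967 = 1.90, which is about 6%. In the everyone-twice simulation it was 7-12%.

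**4. How often exit surveys would repeat.** Under random sampling of n surveys from N patients, the share from someone sampled at least twice is about 1 − exp(−n/N). The analytic minimum is n = 4,000/34 = 118; the facility-feedback sample is n = 300-400.

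| Clinic size | n = 118 | n = 300 | n = 400 |
|---|---|---|---|
| 500 | 21% | 45% | 55% |
| 5,000 | 2.3% | 6% | 8% |
| 10,000 | 1.2% | 3% | 4% |

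**The case against.** The strongest reply is that TEC was never meant to have repeats. The appendix calls it cross-sectional, the SAP counts patients and names the individual as the unit of analysis, and protocol 8.6.1 pairs one person with one encounter. On that reading the facility-only model is adequate. The 50-for-100 figure in section 9.0 fits none of the planned sizes (2,040 in section 8.6.1, 1,360 in Tables 5 and 6, 1,200 in the SAP) and does not establish an expected rate of two. SAP 5.2 analyses every recorded visit, so repetition is inherent there in a way it is not for a small survey. The later SAP also does not list exit surveys as an outcome.

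Most of this stands. It limits the size of the problem for TEC but does not close the gap: section 7.0 permits repeats for experience outcomes, nothing withdraws that, and none of these texts covers exit surveys, which sample every kth patient throughout the study.

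A reader might infer that the planned confidence intervals are wrong, or that false positives are inflated. The documents do not support that. They say only that repeats are possible and give no rate. The case section 7.0 names, repeats before and after crossover, errs on the conservative side. Serious inflation needs most people to be surveyed twice in the same clinic and period; everyone twice would mean about 600 people where the SAP table counts 1,200.

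**Conclusion.** The plan permits repeat experience surveys and does not model them, although it models the same feature for missed visits. If repeats occur, the standard error can be wrong in either direction. On the TEC layout a 25% repeat share matters by about 3-6%, and the extremes are about 17-18% too small and 26% too large. With no repeats there is no error. These sizes rest on assumed repeat shares and an assumed within-person correlation of 0.3-0.5.

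For TEC the practical effect may be small. Exposure is clearer for the protocol's exit-survey analysis: about 21-55% of surveys from repeat respondents in a 500-patient clinic, but only 1-4% in a 10,000-patient clinic, assuming random sampling. The remedy is specific and cheap, so the change is worth making.

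**What to change.** - State in SAP 4.0 and protocol 8.6 whether a patient may enter the TEC or exit analysis more than once, and reconcile section 7.0 with Figure S1, the SAP 4.0 table, section 8.6.1 and section 9.0.
- Link surveys to people by ART number, which section 8.2.2 collects at exit surveys, or by the study enrolment record. For trained-exit patients no ART-number collection is stated and section 9.3 rules out identifiable data in those procedures, so the enrolment record, which their written consent implies, is the likelier route.
- Report distinct people and surveys per person, by condition.
- Where repeats exist, add a patient random intercept nested in facility, as SAP 5.2 does.
- If that term does not converge, or surveys cannot be linked, use facility-level cluster-robust variance with a small-sample correction (TEC has 16 facilities). This covers correlation within a person without identifying the person. Restricting to one survey per person is not an option without linkage, because the repeats cannot be found.

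The cost is one ID merge and one variance term. With few repeats and binary answers that term may be poorly estimated, which is why the robust fallback should be named in advance.

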## **8.0 METHODOLOGY**

## 8.1 Study Objectives

### 8.1.1 Study Design for Objective 1

Objective 1 is a mixed method evaluation of the implementation of the three components of the intervention (i.e., implementation outcomes). As such, it seeks descriptive epidemiological and qualitative findings. We will capture the occurrence of implementation activities (e.g., training, coaching visits, incentive schema) through structured and semistructured electronic forms. This aim also utilizes a combination of in-depth qualitative interviews with patients, focus group discussions (FGDs) with HCWs, records kept by coaches and data collection staff members, and direct observations. The first component includes measurements of patient experience and outcomes which will be used both to inform the nature of coaching and improvement processes at each facility, and what we will use to understand the effects of the intervention. Because we are measuring implementation of the intervention, this will take place at the intervention facilities only.

The ability to understand the extent to which procedures to measure experience and outcomes, as well as interventions to influence them, were carried out will be critical to understanding their effects (or lack thereof). We will capture these quantitatively with “cascade” analyses which describe the implementation process as a series of steps and then quantify the extent to which those steps were met.

### 8.1.2 Study Design of Objective 2

In objective two, we examine the effect of the PCC intervention on patient experience outcomes and service delivery outcomes using a stepped wedge, cluster randomized trial design. As described above, we plan to roll out the intervention in approximately 34 healthcare facilities. These facilities will be stratified by size and geography to ensure balance of facilities types and locations over time and across intervention conditions. Within strata, facilities will be randomly allocated to one of four waves. Each six months, the intervention will be introduced in one of the four waves at time zero, 6, 12 and 18 months. We plan a total of 24 months of follow-up time. The outcomes for this objective are patient experience (e.g., exit interviews) and metrics of service delivery (e.g., completeness of viral load monitoring and trained patient exit interviews). Measurements will be made continuously during the study period. We will estimate the effect using “vertical” approach in which period specific estimates are combined without explicit model specification. The outcomes will be differences across these patient experience and service delivery metrics.

### 8.1.3 Study Design of Objective 3

Objective three examines the effect of the PCC intervention on clinical *care* and clinical outcomes of retention and viral suppression using the same stepped-wedge cluster randomized design. Because retention and viral load are outcomes that may take longer to influence, we design the stepped wedge to weight the first and last steps (which will receive ~ 75% of the facilities), and therefore increase the periods of time where the potential effects on retention and viral suppression can take place. In the design, we will have 18 months of contemporaneous observation time in which some facilities are experiencing the intervention and some the control. We will seek to measure the effect of the intervention one year after patients are exposed to it, which allows a cohort of all patients getting HIV care or treatment at the selected facilities who have encounters over the first six months of observation in waves one and four to accrue at least one year of observation time. Retention will be measured using routine clinic data extracted for the cohort of patients, and our primary outcome will be missing a clinic visit by 14 or more days using stratified Kaplan Meier estimates. We will explore alternative metrics of retention as secondary outcomes including time in care (i.e., the fraction of follow up time compliant with the appointment schedule, medication possession ratio and visit adherence). Given the importance of documentation of clinical and pharmacy appointments and visits, including in community based care, we will support the sites to ensure high performance of normal systems to document and track these data including tracing related outcomes from LTFU

patients. We will also assess viral load one year after exposure to the intervention in a cohort of patients with an encounter at the facility between time zero and 6 months (to be measured between 12 and 18 months). A baseline viral load will also be collected in the cohort between time zero and 6 months from intervention and control sites. Our cohort of viral load participants will include new ART , already on ART ,late/LTFU. Viral load monitoring is now standard, and we will assist facilities (through their normal patient monitoring practices) to complete MOH required monitoring schedules. In addition, we will leverage on existing patient tracing at the facility to assess mortality. We will examine differences in the proportion virally suppressed (at a cut off of 400 copies /ml) using a simple t-test.

#### 8.1.4 Study Design of Objective 4:

Objective four evaluates the cost-effectiveness of the PCC intervention, from both a health systems and a patient perspective. While much of the implementation costs will occur at the central level, many costs of delivery, quality assurance/improvement, and changes in activities are likely to occur at the clinic level. Thus, while much of the costing of PCC implementation can be accomplished through key informant interviews, much of the evaluation of the other components may require observation, interview, or documentation at the clinic level. Our costing activities are designed to comprehensively assess costs that are associated with implementation of the PCC intervention, thereby enabling us to estimate costs of similar programs that might be implemented at different scales, using some (but not all) of the different components, and/or in different epidemiological/economic contexts. We will collect costs in three different manners: (a) one-time, centrally, among PCC staff; (b) one-time, at each of the 34 clinics; and (c) once per wave of the stepped wedge trial, in each of between four to eight clinics that will be purposively sampled to provide a range of urban/rural status, healthcare system level, staffing ratio (e.g., number of vacant positions), geography, and patient volume.

[figure not shown]

#### 8.2 Study Population for Objective 1

Since objective 1 is to understand the extent to which each of the intervention was implemented, the study population for Objective 1 depends on each of three intervention components and will be carried out at each of

the sites implementing the intervention. Because most of the measurements included in the PPEMS are a part of the intervention as well as the outcome (that is to say, the exit interview at a given time will be used to inform the intervention as well as at a later time represent the effects of the intervention), we include an understanding of their implementation in this objective, but it should be clear that we will measure implementation of the relevant parts of the PPEMS in the non-intervention settings to ensure the completeness of outcome ascertainment.

*Table 1: Schema showing measurement schedule for Objective 1*

|        | Period 1                                     | 2                                            | 3                                            | 4                                            |
|--------|----------------------------------------------|----------------------------------------------|----------------------------------------------|----------------------------------------------|
| Wave 4 | PPEMS                                        | PPEMS                                        | PPEMS                                        | PPEMS + Training
coaching +
incentives |
| Wave 3 | PPEMS                                        | PPEMS                                        | PPEMS + Training
coaching +
incentives | PPEMS + Training
coaching +
incentives |
| Wave 2 | PPEMS                                        | PPEMS + Training
coaching +
incentives | PPEMS + Training
coaching +
incentives | PPEMS + Training
coaching +
incentives |
| Wave 1 | PPEMS + Training
coaching +
incentives | PPEMS + Training
coaching +
incentives | PPEMS + Training
coaching +
incentives | PPEMS + Training
coaching +
incentives |

